### Participant timeline {13}

The SPIRIT figure is presented in Fig. 3, which provides an overview of the schedule of enrolment, interventions, and assessments. Figure 4 shows the timeline diagram.

**Fig. 3 Fig3:**
[figure not shown]
SPIRIT figure

**Fig. 4 Fig4:**
[figure not shown]
Timeline diagram

### Sample size {14}

This study uses a randomized, non-blinded, two-armed study design with three times measurements during the study. The power calculation is based on the primary outcome measure- dietary diversity score. The sample size was calculated according to the repeated-measures formula [24, 25]: *N* = $$\frac{2{({{\text{Z}}}_{1-\mathrm{\alpha }/2}+ {{\text{Z}}}_{1-\upbeta })}^{2} {\upsigma }^{2}}{k{\updelta }^{2}}$$. In this formula, parameters denoting the number of repeated times *k* = 3, type I error rate *α* = 5% (two-sided), and a power level of 0.80. We set the smallest detected meaningful difference *δ* = 2.3 according to experts’ experience. Based on the results of relevant studies and our baseline survey, the correlation coefficient among measures *ρ* = 0.7, and equal standard deviation *σ* = 6.12 was used [24, 26]. It was estimated that the desired number of included participants at baseline should be set at a minimum of 60 for each arm. Consequently, a total of 150 community-dwelling elderly individuals are expected to recruit at baseline considering an attrition rate of 20% [27–29].

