### Plans to promote participant retention and complete follow-up {18b}

We will employ several retention strategies to minimize attrition. They include (1) confirming contact information at each assessment and obtaining contact information of two or more people who will know how to contact them; (2) providing a token of appreciation for each assessment, in addition to a small bonus gift for completing all assessments;(3) maintaining a carefully detailed tracking system with the information from both surveys and primary care center records to schedule follow-up assessments and to keep track of other retention efforts such as giving out small gifts; (4) providing daily necessities and health education materials helpful to healthy aging valued at around ¥100 (US $15) will be offered as compensation per assessment to encourage engagement and adherence of participants. In addition, we have conservatively estimated a 20% retention rate at the follow-up assessment for each study arm based on the high reported attrition rates in previous digital health interventions.

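### The 60 per arm in the sample size section cannot be reproduced from its own formula and inputs, so the stated 80% power is unsupported

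*Protocol article*

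**What the plan says.** Sample size {14} of the protocol article sizes the trial on the dietary diversity score (DDS). It opens with "This study uses a randomized, non-blinded, two-armed study design with three times measurements during the study" and prints N = 2(z₁₋α/₂ + z₁₋β)²σ²/(kδ²), with k = 3, a two-sided 5% type I error rate and "a power level of 0.80". The other inputs are given as follows: "We set the smallest detected meaningful difference *δ* = 2.3 according to experts’ experience"; "the correlation coefficient among measures *ρ* = 0.7"; "equal standard deviation *σ* = 6.12 was used". The result is that "the desired number of included participants at baseline should be set at a minimum of 60 for each arm", which is then raised to 150 in total for 20% attrition.

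Section {18b} describes the same loss to follow-up the other way round: "we have conservatively estimated a 20% retention rate at the follow-up assessment for each study arm".

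Two other sections bear on which calculation would fit. Outcomes {12} defines the primary outcome as change from T0 to T1 (3 months) and T2 (6 months). Statistical methods {20a} plans generalized linear mixed models with intervention and time as the main fixed effects, participant random effects and a list of confounders. That list includes diet, undefined, but does not name the baseline DDS.

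**The concern.** The formula, every input and the answer stand in one paragraph, and they do not agree. One input, ρ, is quoted with a value but has no place in the formula. Leaving it out amounts to assuming that three scores from the same person carry as much information as scores from three different people, which contradicts a stated correlation of 0.7. In addition, k = 3 can only mean T0, T1 and T2, so the formula averages the intervention effect over an occasion that precedes the intervention.

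This is the only power justification in the article, and it concerns the outcome that sizes the trial. If the 80% cannot be traced to a calculation, a reader of a null DDS result cannot tell whether a difference of 2.3 was reasonably excluded or was never likely to be detected.

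**Working it through.** **Inputs, all from {14}:** z₀.₉₇₅ = 1.960, z₀.₈₀ = 0.842, σ = 6.12, δ = 2.3, k = 3, ρ = 0.7, attrition 20%.

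**Common term (one measurement per person):** 2 × (1.960 + 0.842)² × 6.12² / 2.3² = 111.14 per arm.

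**The plan's figure.**
- Formula as printed: 111.14 / 3 = 37.05, so 38 per arm. The plan states 60.
- With ρ inserted under equal correlation, the factor is 1 + (3 − 1) × 0.7 = 2.4. Then 37.05 × 2.4 = 88.9, so 89 per arm. Again not 60.
- Correlation that would give 60: 60 / 37.05 = 1.62, and (1.62 − 1) / 2 ≈ 0.31. Using 0.3 (that is, 1 − 0.7) gives 37.05 × 1.6 = 59.3, which may or may not be how 60 arose. It contradicts the stated 0.7 in any case.
- Attrition step: 60 / 0.8 = 75 per arm, 150 in total. This step does reproduce.

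**Power at 60 completers per arm.** Let f be the variance of the analysed quantity divided by σ². Then n = 111.14 × f and power = Φ(2.3 / (6.12 × √(2f/60)) − 1.960). For f = 1 the ratio inside Φ is 2.3 / 1.117 = 2.058; for other f it is 2.058 / √f.

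| Analysis | f with ρ = 0.7 | n per arm for 80% | Power at 60 |
|---|---|---|---|
| Printed formula (independence, three occasions) | 1/3 = 0.333 | 37.05 | 95% |
| Three-occasion average with ρ | 2.4/3 = 0.80 | 88.9 | 63% |
| Mean of T1 and T2, unadjusted | (1 + ρ)/2 = 0.85 | 94.5 | 61% |
| Change from T0 at one follow-up | 2(1 − ρ) = 0.60 | 66.7 | 76% |
| ANCOVA at one follow-up | 1 − ρ² = 0.51 | 56.7 | 82% |
| Mean of T1 and T2 minus T0 | (1 + ρ)/2 + 1 − 2ρ = 0.45 | 50.0 | 87% |
| Mean of T1 and T2 adjusted for T0 | (1 + ρ)/2 − ρ² = 0.36 | 40.0 | 93% |

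The first two rows assume the full difference of 2.3 at T0 as well as at T1 and T2, so neither describes this design. The last five use T0 only as a reference or covariate, or not at all. They span 61% to 93% with the same σ, δ and ρ.

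**The case against.** The strongest reply is that failing to reproduce a number does not show that the number is too small. This stands. Analyses that use the baseline score fit the definition of the primary outcome in {12} better than an average over three occasions does, and several of them give at least 80% at 60 per arm: 82%, 87% and 93%. ANCOVA at one follow-up needs 57 per arm, or 58 with a t-correction, which is close to 60. It does not rescue the derivation, because it uses no k = 3 and is not the formula that {14} says was applied.

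A reader might go further and infer that the trial is underpowered at individual level and should enrol 89 / 0.8 = 112 per arm, 224 in total. The documents do not support that. The 89 and its 63% assume an effect of 2.3 at T0, before any intervention. If T0 carries no effect, the three-occasion average effect is 2/3 × 2.3 = 1.53, and power on that average falls to about 34%. The 89 shows only that the stated ρ does not lead to 60; it is not a target for this design.

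A reader might also take the 20% retention in {18b} literally and conclude that 0.2 × 75 = 15 per arm would remain. That is not the meaning. The same sentence appeals to high attrition in earlier studies, {14} says 20% attrition, and 60 / 0.8 = 75 confirms it. It is a slip of wording.

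Finally, an article condenses a fuller protocol. That would excuse a missing derivation, but not a printed formula, inputs and result that disagree with one another.

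**Conclusion.** The concern holds in this form: 60 per arm for 80% power follows neither from the printed formula (38) nor from that formula with the stated correlation inserted (89). ρ = 0.7 is listed but unused, and baseline is counted as an outcome occasion. The 80% is unsupported as written. Whether the true individual-level power is lower or higher cannot be settled from {14}. It runs from about 61% to about 93% according to how T0, T1 and T2 enter the analysis, and {20a} does not state that the baseline DDS is a covariate, so the favourable end cannot simply be assumed.

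These figures rest on the plan's own σ, δ and ρ, equal variance and equal correlation across occasions, a difference of 2.3 at each follow-up, 60 completers per arm and the normal approximation. They ignore the cluster randomisation of six sites, which is a separate matter to be applied on top and is not needed for this conclusion.

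**What to change.** In {14}, replace the formula with one that contains ρ, uses the post-baseline measurements and matches the planned analysis model. One example is the mean of T1 and T2 with T0 as covariate: n = 2(z₁₋α/₂ + z₁₋β)²σ²[(1 + ρ)/2 − ρ²]/δ², about 40 per arm with the stated inputs. Other choices are acceptable if the model in {20a} agrees with them. Print the N that the chosen formula gives, and restate the power for 60 completers per arm (150 enrolled); under the example this is about 93% before clustering.

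In {18b}, change 20% retention to 20% attrition so that it agrees with {14}.

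The cost is a rewrite of one paragraph, a one-word correction and a changed power statement. This point by itself requires no change in enrolment.

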### Trial design {8}

This experimental study expected to run from July 2023 to September 2024 will follow a non-blinded, paralleled, two-arm pre-test post-test design including 150 community-dwelling elders. This trial will be conducted simultaneously in six community health service centers within Nanhu district, Jiaxing City, located in Zhejiang province, China. Following a cluster randomization design, intervention and control sites will be allocated in a 1:1 ratio based on a randomized allocation sequence generated by a single investigator using R 4.2.0 The intervention period is expected to last for 6 months, following a preparation and recruitment phase. Effect measurements will be conducted at three time points: at the beginning, after 3 months, and after 6 months of the intervention. Implementation measurements will be carried out throughout the study. The trial design follows the SPIRIT checklist (Additional file 1).

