### Implementation {16c}

An investigator will use a randomization algorithm to allocate six candidate sites to different groups, ensuring random and unbiased assignment. The results will be informed to the social workers at respective sites. At each site, social workers will be responsible for recruitment and conducting baseline assessments. All subjects who have provided informed consent will be included in the trial. The social workers will guide the enrollment session, explaining the intervention assignment process to the participants. Following enrollment, the overarching purpose of the study, intervention procedures in the assigned group, and measurement details will be thoroughly explained to each participant. Additionally, each participant will undergo a baseline assessment that includes collecting information on socio-demographics, dietary behaviors, anthropometric characteristics, medical history, and nutritional status.

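### The sample size is worked out for randomised individuals, but six sites are randomised, so the stated 80% power does not belong to this design

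*Protocol article*

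**What the plan says.** Three sections of the protocol article make the site the unit of randomisation. Trial design {8}: "This trial will be conducted simultaneously in six community health service centers within Nanhu district", with intervention and control sites allocated 1:1. Sequence generation {16a} repeats that the design is cluster randomised. Implementation {16c}: "An investigator will use a randomization algorithm to allocate six candidate sites to different groups". Six sites at 1:1 means three per arm.

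Sample size {14} describes the trial only as randomised, non-blinded and two-armed. "The sample size was calculated according to the repeated-measures formula", namely N = 2(Z₁₋α/₂ + Z₁₋β)²σ²/(kδ²), with k = 3 and "type I error rate *α* = 5% (two-sided), and a power level of 0.80". The other inputs are "We set the smallest detected meaningful difference *δ* = 2.3 according to experts’ experience", "equal standard deviation *σ* = 6.12 was used" and "the correlation coefficient among measures *ρ* = 0.7". The result is at least 60 per arm, and then "a total of 150 community-dwelling elderly individuals are expected to recruit at baseline considering an attrition rate of 20" per cent.

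Statistical methods {20a} plans generalised linear mixed models. The random effects it describes are for variation between individuals; no site effect is named.

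**The concern.** The formula in {14} treats participants as independent. It contains no ICC, cluster size, number of clusters or design effect. The one correlation quoted, 0.7, is between repeated measures on the same person, and it does not appear in the printed formula. The only inflation is for attrition.

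People at one site share a community and a canteen, and the primary diet scores come from dishes logged at checkout, so some similarity within sites is plausible. It would inflate the variance of the arm difference. With three sites per arm there is also little information from which to estimate between-site variation. Readers would take the trial to be 80% powered for a difference of 2.3 when the calculation does not show that for the trial being run.

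**Working it through.** **Inputs.** From {14}: δ = 2.3, σ = 6.12, k = 3, ρ = 0.7, two-sided α = 0.05, power 0.80, 60 per arm, 20% attrition. From {8} and {16c}: six sites, three per arm. Assumed, because the protocol does not give them: ICC of 0.01 to 0.10; equal site sizes (150/6 = 25 enrolled and 60/3 = 20 completers per site); and, where stated, a site-level test on 6 − 2 = 4 df.

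**Step 1: the plan's own figure.**
- One measure: 2(1.960 + 0.842)² × 6.12²/2.3² = 111.1 per arm.
- Printed formula: 111.1/3 = 37.05, so 38 per arm.
- Usual form using ρ: 111.1 × (1 + 2 × 0.7)/3 = 88.9, so 89 per arm.
- Neither is 60. Only the last step reproduces: 120/0.8 = 150. That step uses up the whole increase, so no allowance for clustering is contained in going from 120 to 150.

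**Step 2: design effect.** DE = 1 + (20 − 1) × ICC. The effective sample is 120/DE.

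**Step 3: power.** A design with exactly 80% power has expected test statistic 1.960 + 0.842 = 2.802. Clustering divides it by √DE. For a baseline-adjusted analysis (one baseline, mean of two follow-ups) the variance factor is (1 + 0.7)/2 − 0.7² = 0.85 − 0.49 = 0.36. The statistic is then 2.3/(6.12 × √0.36 × √(2/60)) = 3.43, or 93% power if people are independent. I apply the same DE to both, so for the adjusted rows the ICC is that of adjusted scores. The t test uses the non-central t with critical value 2.776.

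| | ICC 0.01 | 0.02 | 0.05 | 0.10 |
|---|---|---|---|---|
| Design effect | 1.19 | 1.38 | 1.95 | 2.90 |
| Effective sample of 120 | 101 | 87 | 62 | 41 |
| Nominal 80%, normal | 73% | 67% | 52% | 38% |
| Nominal 80%, t on 4 df | 50% | 44% | 34% | 25% |
| Baseline-adjusted, normal | 88% | 83% | 69% | 52% |
| Baseline-adjusted, t on 4 df | 66% | 60% | 47% | 34% |

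**Step 4: how far the starting point matters.** With 60 completers per arm and ICC = 0:

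| Variance used | Normal | t on 4 df |
|---|---|---|
| Printed formula | 95% | 76% |
| Baseline-adjusted | 93% | 73% |
| 60 taken as the 80% number | 80% | 56% |
| ρ = 0.7 in the usual form | 63% | 42% |

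**Step 5: the {20a} model fitted with participant effects only.** The standard error is then too small by a factor of √DE. The two-sided false-positive rate is 2 × [1 − Φ(1.960/√DE)], which is about 7%, 10% and 16% at ICC 0.01, 0.02 and 0.05. From a nominal 80%, the chance of rejecting under a true difference of 2.3 is about Φ(0.842/√DE), or 78%, 76% and 73%.

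**Step 6: more participants in the same six sites.** Keeping 60 effective participants per arm with three sites needs m = 20(1 − ICC)/(1 − 20 × ICC) completers per site. At ICC 0.01, m = 24.75, or about 75 per arm. At 0.02, m = 32.7, or 98 per arm. At 0.05 the denominator is zero and no number is enough.

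**The case against.** A reader might infer that 150 participants cannot reach 80% power. The protocol does not support that as a flat statement. It gives no ICC and no site quota, and {20a} names no degrees-of-freedom method, so the 4 df describe a defensible site-level analysis and not one the protocol states. With a normal reference, the baseline-adjusted analysis stays above 80% at ICC 0.01 and 0.02. Read literally, the printed formula needs only 37.05 per arm, so 60 contains slack of 60/37.05 = 1.62. That would absorb an ICC up to (1.62 − 1)/19, about 0.033, under a normal reference. These points stand as limits on how firmly the shortfall can be sized.

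The slack does not rescue the claim. The protocol does not offer it as a design effect; it exists only if three measures correlated at 0.7 count as independent; and it is gone on 4 df, where that variance gives 76% even at ICC = 0.

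A reader might also infer that the chief danger is a missed effect. Under the model as described, with participant effects only, it is a false positive. The loss of power appears once site is properly accounted for. A fuller analysis plan may do that, but it would not make the printed power right.

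Nor does it follow that enrolling more people within the six sites is futile. That holds only at an ICC of about 0.05 or higher.

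**Conclusion.** The concern holds. Section {14} prints a complete calculation for independent individuals, while {8}, {16a} and {16c} randomise six sites, so the 80% is not the power of this design. This is a contradiction within the article, not a detail left to another document.

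The mismatch itself needs no assumption; its size does. Over the assumed ICCs, power runs from 88% down to 38% with a normal reference and from 66% down to 25% on 4 df, depending on the variance used. The starting point is itself unsettled, since 60 per arm follows neither from the printed formula (38) nor from the form using ρ (89). With 60 completers per arm on 4 df, all four variance versions fall below 80% even at ICC = 0 (42% to 76%), and any positive ICC lowers them.

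**What to change.** - **Sample size {14}:** state that the trial is cluster randomised with three sites per arm. Give an assumed ICC range with its source, the expected number per site, the design effect and a small-sample df. Restate the power, or the detectable difference, for 150 participants in six sites, and withdraw the unqualified 80%. If the baseline survey is used for the ICC, say whether it covered these sites; an estimate from six clusters would be very imprecise, so a range is still needed.
- **The same calculation:** show how 60 per arm arises, since the restated power depends on it.
- **Statistical methods {20a}:** account for site, with a small-sample method suited to six clusters.
- **Limitations in the Discussion:** add the small number of randomised sites.

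This is rewording plus one change to the model. It requires no new participants or procedures. The cost is a less favourable stated power.

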### Recruitment {15}

A convenience sampling method will be used to recruit community-dwelling elders from six communities mentioned in section {8}. Patients will be primarily recruited through three methods: (1) posting flyers at primary care centers during regular physical examinations of community-dwelling elderly individuals, (2) recommendations from community healthcare professionals during clinical appointments at community health service centers, (3) recommendations during community healthcare professionals’ regular home visits with elderly individuals. Additionally, the staff of the community health service center sent recruitment messages. We expect the physical examination to serve as the primary recruitment channel. Trained social workers will assist potentially eligible patients in confirming their eligibility. Eligible elderly individuals will receive invitations to attend the enrollment session, during which the social workers will provide instructions on participation procedures, and interested individuals will be given a consent package.

## Assignment of interventions: allocation

### Sequence generation {16a}

Under the cluster randomization design, one investigator will generate a randomized allocation sequence using R 4.2.0 to allocate the intervention and control sites at a 1:1 ratio. The investigator tasked with generating the randomization sequence is specifically chosen for non-involvement in the recruitment of centers or the collection of participant data.

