## Methods: participants, interventions, and outcomes

### Study setting {9}

The study settings will be established in six community health service centers, strategically located in distinct geographical areas within the Nanhu district. These centers were chosen for their accessibility and convenience for device deployment. The participants are expected to be residents of these respective communities. In this trial, the healthcare professional team consisted of informatics scientists from the Institute of Medical Information, nutrition scientists from Chinese Center for Disease Control and Prevention, and clinicians from Peking Union Medical College Hospital. Participant recruitment and outcome measurements will be performed in the community centers, where community health service centers and elderly-serving canteens are located.

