### Concealment mechanism {16b}

Due to the utilization of a cluster randomization method, we do not conceal the allocation. As a result, the proposed concealment mechanism is not applicable in this scenario. The allocation sequence will be securely concealed and not disclosed until all centers are recruited and baseline data are collected.

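### Six sites are split 3:3 with no balancing rule beyond the 1:1 ratio, so there is a substantial chance (about 25–53%) of a baseline DDS gap of half the target effect, and the stated model names no baseline-score covariate

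*Protocol article*

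**What the plan says.** The unit of allocation is the site. Sequence generation {16a}: "one investigator will generate a randomized allocation sequence using R 4.2.0 to allocate the intervention and control sites at a 1:1 ratio". Implementation {16c}: "An investigator will use a randomization algorithm to allocate six candidate sites to different groups, ensuring random and unbiased assignment". Trial design {8} repeats the 1:1 cluster allocation. None of the three names a stratum, a matching factor or a balance criterion. Study setting {9} describes the centres as "strategically located in distinct geographical areas within the Nanhu district" and reports no site-level figures.

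The timing is stated in two ways. Concealment mechanism {16b} says "The allocation sequence will be securely concealed and not disclosed until all centers are recruited and baseline data are collected", but also "Due to the utilization of a cluster randomization method, we do not conceal the allocation". Implementation {16c} says of the allocation "The results will be informed to the social workers at respective sites", and then "At each site, social workers will be responsible for recruitment and conducting baseline assessments".

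Statistical methods {20a} gives intervention and time as the primary fixed effects, with random effects for individual variation. The confounders listed are age, gender, education, physical activity, diet, smoking and medication. The T0 value of the outcome is not explicitly among them, and no intervention-by-time term is named. Outcomes {12} defines the primary outcome as change from T0 to T1 and T2.

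**The concern.** A plain 1:1 draw is a valid randomisation, but with three sites per arm it gives little assurance that the arms start level. If the arms differ at T0 by an amount comparable to the target effect, and the model does not condition on T0, that difference competes with the intervention as the explanation of the result. {16a} is the place where a balancing rule would be stated. The draw comes before any analysis, so a statistical analysis plan cannot supply the rule later.

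**Working it through.** **Inputs.** From Sample size {14}: σ = 6.12, δ = 2.3 (half is 1.15), within-person correlation ρ = 0.7, 60 per arm before attrition, 150 in total. From {16c}: six sites. Assumptions: equal site sizes, normal site means, and ICC 0 to 0.10.

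**The plan's own figures.** 60/(1 − 0.20) = 75 per arm and 150 in total, which reproduces. This gives 150/6 = 25 per site. The printed formula gives 2(1.96 + 0.8416)² × 6.12²/(3 × 2.3²) = 37.05 per arm, not 60. That is a separate matter; what follows uses only 150, 6.12, 2.3 and 0.7.

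**Size of a chance T0 gap.** SD of a site mean = 6.12 × √(ICC + (1 − ICC)/25). SD of the arm difference = that × √(2/3). Tail probabilities are normal. The last column is the person-level share of the variance, [(1 − ICC)/25]/[ICC + (1 − ICC)/25].

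| ICC | SD of gap | P(gap ≥ 1.15) | P(gap ≥ 2.3) | Person-level share |
|---|---|---|---|---|
| 0 | 1.00 | 25% | 2% | 100% |
| 0.02 | 1.22 | 34% | 6% | 66% |
| 0.05 | 1.48 | 44% | 12% | 43% |
| 0.10 | 1.84 | 53% | 21% | 26% |

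The probability reaches one half when the SD is 1.15/0.6745 = 1.705, that is at ICC = [1.705² × 75/(2 × 6.12²) − 1]/24 ≈ 0.08.

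**What a gap of 1.15 does to the estimate.** Two extremes bracket it. A pure person-level gap regresses to 0.7 × 1.15 = 0.805 at follow-up. A fully stable site gap stays at 1.15.
- Intervention main effect over T0, T1 and T2, no baseline covariate: (1.15 + 2 × 0.805)/3 = 0.92, up to 1.15. That is 40–50% of δ.
- Change from T0: 0.805 − 1.15 = −0.345, up to 0.
- T0 as covariate with slope 0.7: 0, up to 0.3 × 1.15 = 0.345, at most 15% of δ.

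**What restriction can do.** There are C(6,3) = 20 allocations, which form 10 distinct partitions. Each pair of sites is together in 4 partitions and apart in 6. Keeping 14 allocations keeps 7 partitions. Since 7 exceeds both 4 and 6, no pair can be always together or always apart. Keeping only 10 allocations (5 partitions) carries no such guarantee. In 20,000 simulated sets of six site means, some pair was always together or always apart in 63% of sets when balancing on one score and 56% on two independent scores.

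Simulated P(gap > 1.15) on DDS (100,000 sets of six site means, all 10 partitions):

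| ICC | No restriction | Best 14 of 20 | Best 10 of 20 |
|---|---|---|---|
| 0.02 | 34% | 14% | 4% |
| 0.05 | 44% | 24% | 9% |
| 0.10 | 53% | 35% | 18% |

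These figures are for balancing on DDS alone. With a second, independent score given equal weight, the best 14 of 20 give 22%, 32% and 43% for DDS. If DDS and CDGI-E are positively correlated, the figures would be expected to lie between the two sets.

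**The case against.** The strongest reply is that nothing in {16a} is misstated: a random 1:1 draw is unbiased over repetitions, and constrained randomisation is an optional gain. A T0 gap is also not itself an error in the effect estimate. The primary outcome is change from T0, and a stable site difference largely cancels in a change score. Both points are right. What they leave open is that {20a} names neither the T0 score as a covariate nor an intervention-by-time term, and the entry for diet among the confounders is undefined. The estimate is therefore protected under one reading of the protocol and exposed under another.

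Three stronger readings are tempting, and the document does not support them.
- A reader might infer that a gap of half the target is likely. That needs an ICC of about 0.08 or more, and no ICC is given.
- A reader might infer that the sites are known to differ. The protocol says only that they lie in separate areas of one district. It reports no difference in diet or population, and much of the risk at low ICC is person-level sampling, which larger site samples would reduce.
- A reader might infer that the gap is simply avoidable because baseline precedes disclosure. {16b} does say "not disclosed until all centers are recruited and baseline data are collected", but {16c} has the social workers told the result and then made responsible for recruitment and baseline assessment. Disclosing a sequence after baseline also does not mean generating it after baseline.

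**Conclusion.** The point holds as a material, reducible risk. For six sites allocated 3:3 with no stated balancing rule, the chance of a T0 DDS gap of at least 1.15 is about 25–53% over ICC 0–0.10, and of a gap as large as the full 2.3 about 2–21%. These figures rest on 25 people per site, normality and an assumed ICC. That no restriction applies is read from the absence of one in {8}, {16a} and {16c}. A gap of 1.15 could move the estimate by 0.92–1.15 if the intervention main effect is read across all three visits without baseline adjustment, and by at most about 0.35 in either direction if T0 is used. It does not follow that the result will be biased, or that balancing would remove the problem.

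**What to change.** 1. Reconcile {16b} and {16c}. State once whether allocation is concealed, and have the sequence generated, not merely disclosed, after T0 data are complete at all six sites.
2. In {16a}, have the uninvolved investigator list the 20 allocations, score each for balance in site-mean T0 DDS and CDGI-E, and draw one at random, with a recorded seed, from the 14 better balanced. If the draw cannot follow T0, score balance on site characteristics known beforehand; the gains shown above would then not apply as computed.
3. In either case, and also if the draw has already been made, add the T0 value of the outcome and the balancing variables to the model in {20a}. T0 is already collected, so this costs nothing in data.

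The cost is a short R script and a rewrite of {16a}–{16c} together. The downside is fewer possible allocations: the smallest two-sided permutation p rises from 2/20 = 0.10 to 2/14 = 0.14. No 5%-level permutation test exists with 3 v 3 in any case.
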